While a few clinical trials have been published in Japan, they were not RCTs. Moreover, the results derived from Japanese denture wearers might be different from those mentioned in previous studies performed in other countries since patients’ attitudes toward dental materials reflect food culture and socioeconomic differences among the countries. Therefore, guidelines or official statements concerning the use of denture adhesives in clinical practice in Japan cannot be developed at this time. Performing RCTs and collecting data that can be used to develop clinical practice guidelines to standardize the usage, raise the quality of care, and reduce the risk for older Japanese individuals is essential, since there are many older individuals in Japan who cannot receive denture treatment in a dental clinic owing to their physical conditions, meaning they may turn to dental adhesives instead. Thus, we plan to perform an RCT at the following ten centers: Iwate Medical University, Tohoku University, Tokyo Medical and Dental University, Nihon University School of Dentistry at Matsudo, Tsurumi University, Kanagawa Dental College, Osaka Dental University, Tokushima University, Nagasaki University, and Kagoshima University. This ten-center RCT, which will be performed throughout Japan, has external validity. This trial is referred to as the Denture Adhesive Guideline (DAG) project. The aim of the DAG trial is to verify the efficacy of denture adhesives in order to establish guidelines for using denture adhesives in clinical practice in Japan. The null hypothesis of this study is that the application of two types of denture adhesives (cream and powder) and a control would not produce differences in the set outcomes and would not result in differences in the improvement of the set outcomes between baseline and day 4 following application.

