### Sample size calculation

A between-group difference of 29 mm on the visual analog scale (VAS) ratings for general satisfaction was considered a meaningful difference. By using variances of 20 mm in the intervention groups and 23 mm in the control group, which were based on previously reported data [22, 23], 100 subjects per group, including an assumed dropout rate of 10 %, will be required to achieve 80 % power with an alpha level of 5 %.

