### Interim analyses and early stopping of the clinical trial

The data and safety of the clinical trial will be monitored. Interim analyses of the trial will be performed when 100 and 200 participants have completed the trial. The trial will be stopped under the following conditions: (1) excess harm is observed, (2) statistically significant benefits are observed, (3) little additional useful information or negligible chance of demonstrating efficacy will be yielded if fully completed. These early stopping rules will help minimize harm and maximize the benefits for the patients enrolled in the RCT.

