### Randomization, allocation concealment, and sequence generation

A randomized, controlled parallel clinical trial will be conducted at the abovementioned ten centers. Participants will be randomly assigned to one of the following three groups and will be instructed to apply either a denture adhesive or a control solution to both their maxillary and mandibular dentures: cream-type denture adhesive group, powder-type denture adhesive group, and control group (Fig. 1). Balanced allocation of participants to each group will be achieved using the following method: 300 random allocation numbers with no overlap and no underlap will be generated by the “RAND” and “RANK” functions in Excel (Microsoft Japan Co. Ltd., Tokyo, Japan). The first to 300^th^ numbers will be ordered randomly. Then, the first to 100^th^, 101^st^ to 200^th^, and 201^st^ to 300^th^ randomly ordered numbers will be assigned to the cream-type denture adhesive group, powder-type denture adhesive group, and control group, respectively. As per the assignment, 300 envelopes containing a card stamped with the group name will be prepared. The 300 envelopes will be divided 30 by 30 for ten centers in sequence, which means that each of the ten centers will receive 30 envelopes. Then, the coordinator at each center will open one envelope and allocate a qualifying participant to the indicated group after the patient agrees to participate in the study and provides informed consent. This method enables us to allocate the 300 numbers to the three groups equally and randomly. Once the 300 participants have been completely allocated, the number of participants in each of the three groups will be equal. Blinding the participants to the intervention is not feasible, since the participants will be able to determine the type of denture adhesive they are using during application. Evaluators are blinded to the allocation.

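### The rule that stops the whole three-arm trial for benefit could well end it before 300 patients: above 99.9% at the first look under the printed 29 mm, about 39% (72% by the second look) under the 9 mm that reproduces the sample size

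*Protocol article*

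**What the plan says.** All references are to the protocol article.

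- **Interim analyses and early stopping of the clinical trial:** "Interim analyses of the trial will be performed when 100 and 200 participants have completed the trial". The trial, not an arm, is then to be stopped under any of three conditions: excess harm, "2) statistically significant benefits are observed", or little prospect of further useful information. The section does not say which of the three group comparisons or which outcome counts, and gives no interim critical value.
- **Statistical analysis:** p<0.05 is the only significance threshold. Groups are compared by one-way ANOVA with Tukey-Kramer tests or by a rank-based equivalent. Multiple regression on covariates and subgroup analyses are also planned.
- **Sample size calculation:** "A between-group difference of 29 mm on the visual analog scale (VAS) ratings for general satisfaction was considered a meaningful difference". The spreads are given as follows: "By using variances of 20 mm in the intervention groups and 23 mm in the control group". The result is "100 subjects per group, including an assumed dropout rate of 10" per cent, for 80% power at 5% alpha.
- **Background:** the null hypothesis covers all three groups, namely that "the application of two types of denture adhesives (cream and powder) and a control would not produce differences in the set outcomes".

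**The concern.** The trial has three arms and more than one aim, but a benefit finding ends all of it. If one adhesive beating saline is enough, the easiest contrast decides how many patients are available for the harder ones: cream against powder, the covariate regression and the subgroups. The planning difference is large relative to the spreads, so the rule might fire at the first look as a matter of course. The guideline that the trial is meant to support would then rest on far fewer patients than planned for the comparison between products and for the question of who benefits. The protocol article gives no probability of stopping at either look.

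**Working it through.** **Inputs.** Difference 29 mm; spreads 20 mm (adhesives) and 23 mm (control), read as SDs because the unit is mm although the text calls them variances; 100 per group with 10% dropout, so 90 evaluable; 80% power; alpha 5%, taken as two-sided because sidedness is not stated. Looks are at 100 and 200 completers. The section on randomization promises equal groups at full allocation ("Once the 300 participants have been completely allocated, the number of participants in each of the three groups will be equal"), so about 33 and 66 per arm at the looks is an assumption.

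**Step 1: the plan's own sample size.** n per group = (1.960 + 0.842)² × (20² + 23²) / d² = 7.849 × 929 / d².

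- d = 29: 7291.6 / 841 = 8.67, so 9 per group and 10 with dropout. At 90 per group the power is above 99.99%, not 80%.
- d = 9: 7291.6 / 81 = 90.02, and 90.02 / 0.9 = 100.02. At 90 per group the power is 80.0%.

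The stated 100 per group does not follow from 29 mm. It does follow from 9 mm. Both are carried forward.

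**Step 2: first look, one adhesive-control comparison.** SE = √(20²/33 + 23²/33) = √(929/33) = 5.31 mm. The probability of significance is P(Z > c − d/SE). A critical value of 3.71 stands for a conservative O'Brien-Fleming-type first look.

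| True difference | Expected z | c = 1.96 | c = 3.71 |
|---|---|---|---|
| 29 mm | 5.47 | above 99.9% | 96% |
| 15 mm | 2.83 | 81% | 19% |
| 9 mm | 1.70 | 40% (39% by the t-test) | 2% |

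**Step 3: the planned Tukey test, simulated.** Three normal arms, no interim adjustment, 33 then 66 per arm. The trial stops if at least one adhesive beats control.

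| True effect | Stopped at look 1 | Stopped by look 2 |
|---|---|---|
| 29 mm, both adhesives | above 99.9% | about 100% |
| 9 mm, both adhesives | 39% | 72% |
| 9 mm, one adhesive only | 27% | 57% |

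**Step 4: what a first-look stop costs.** Cream versus powder, SD 20, 95% CI half-width = 1.96 × 20 × √(2/n).

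- n = 90: 5.8 mm.
- n = 33: 9.7 mm.

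The difference detectable with 80% power, unadjusted, is 2.80 × 20 × √(2/n): 8.4 mm at n = 90 and 13.8 mm at n = 33.

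**The case against.** **29 mm is not a reliable basis.** It contradicts the protocol's own sample size, and it is described as a meaningful difference, not as the expected effect. A reader might infer from it that the trial is almost bound to stop at 100 completers. The documents do not support that as a general statement: at 9 mm a first-look stop is less likely than not. This stands, and it is why both differences are shown. Nor do the documents show that 29 is a misprint for 9; that is only an inference from the arithmetic.

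**A proper boundary might be all that is needed.** At 29 mm it would not be, since z = 3.71 is still crossed 96% of the time. At 15 mm the rate falls from 81% to 19%, and at 9 mm to about 2% per comparison. So it is fair to say that a conservative boundary largely removes early stopping at the first look for effects in line with 100 per group. No such boundary is printed, however.

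**The other comparisons are not lost.** A reader might infer that an early stop leaves the cream-versus-powder and subgroup questions undelivered. All three arms are randomized throughout, so every planned analysis can be run on about 100 completers. The loss is in precision. The protocol article also states no power target for cream versus powder.

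**An article may leave the boundary and the triggering comparison to a fuller document.** That is fair, and their absence alone is not the point. The point is that the printed rule ends the whole trial on significant benefit, which has consequences for the other aims under any reading of the effect size.

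**Conclusion.** The point holds, with its size depending on which difference is the real design basis. Under the only threshold printed, stopping before 300 is near certain at 29 mm. At 9 mm in both adhesives it is still more likely than not by the second look (72%), and it is 57% if only one adhesive works. A first-look stop would put the cream-versus-powder, regression and subgroup analyses on about one third of the planned patients, without preventing them. These figures assume that the spreads are SDs, that the arms are about equal at each look, that one adhesive beating control triggers the rule, and that no interim adjustment is made. With a conservative first-look boundary the 9 mm figure drops to about 2% per comparison, while the 29 mm figure stays at about 96%. The conflict between 29 mm and 100 per group is arithmetic and has to be settled before any single stopping probability can be quoted.

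**What to change.** 1. **Interim analyses section:** remove condition (2) as a reason to stop the whole trial, and keep both looks for conditions (1) and (3). Participants counted in a look have already finished their eight meals, so stopping for benefit gives them nothing.
2. **If a benefit rule is kept:** name the outcome and comparison that trigger it, use a group-sequential boundary, and allow a stop only when both adhesive-control comparisons cross it. State the cream-versus-powder precision that would result from a stop at each look.
3. **Sample size section:** reconcile the 29 mm difference with 100 per group and 80% power, and say whether 20 and 23 mm are SDs. Then give the probability of stopping at each look under the reconciled difference.

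The first change is a one-sentence amendment. Its cost is that the trial cannot finish early for benefit; enrolment stays at the 300 already planned.

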### Randomization, allocation concealment, and sequence generation

A randomized, controlled parallel clinical trial will be conducted at the abovementioned ten centers. Participants will be randomly assigned to one of the following three groups and will be instructed to apply either a denture adhesive or a control solution to both their maxillary and mandibular dentures: cream-type denture adhesive group, powder-type denture adhesive group, and control group (Fig. 1). Balanced allocation of participants to each group will be achieved using the following method: 300 random allocation numbers with no overlap and no underlap will be generated by the “RAND” and “RANK” functions in Excel (Microsoft Japan Co. Ltd., Tokyo, Japan). The first to 300^th^ numbers will be ordered randomly. Then, the first to 100^th^, 101^st^ to 200^th^, and 201^st^ to 300^th^ randomly ordered numbers will be assigned to the cream-type denture adhesive group, powder-type denture adhesive group, and control group, respectively. As per the assignment, 300 envelopes containing a card stamped with the group name will be prepared. The 300 envelopes will be divided 30 by 30 for ten centers in sequence, which means that each of the ten centers will receive 30 envelopes. Then, the coordinator at each center will open one envelope and allocate a qualifying participant to the indicated group after the patient agrees to participate in the study and provides informed consent. This method enables us to allocate the 300 numbers to the three groups equally and randomly. Once the 300 participants have been completely allocated, the number of participants in each of the three groups will be equal. Blinding the participants to the intervention is not feasible, since the participants will be able to determine the type of denture adhesive they are using during application. Evaluators are blinded to the allocation.

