**Methods:**

This ten-center, randomized controlled trial with parallel groups is ongoing. Three hundred edentulous patients with complete dentures will be allocated to three groups (cream-type adhesive, powder-type adhesive, and control groups). The participants will wear their dentures with the denture adhesive for 4 days, including during eight meals (three breakfasts, two lunches, and three dinners). The baseline measurements and final measurements for the denture adhesives will be performed on the first day and after breakfast on the fourth day. The primary outcome is a general satisfaction rating for the denture. The secondary outcomes are denture satisfaction ratings for various denture functions, occlusal bite force, resistance to dislodgement, masticatory performance, perceived chewing ability, and oral health-related quality of life. Between-subjects comparisons among the three groups and within-subjects comparisons of the pre- and post-intervention measurements will be performed. Furthermore, a multiple regression analysis will be performed. The main analyses will be based on the intention-to-treat principle. A sample size of 100 subjects per group, including an assumed dropout rate of 10 %, will be required to achieve 80 % power with a 5 % alpha level.

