### Statistical analysis

First, analyses of normality using the Kolmogorov–Smirnov test will be performed for all variables. When normality can be verified, parametric tests will be performed. However, if normality cannot be verified, then two types of analyses will be performed, as follows: (1) the distributions of the dependent variables will be normalized by the appropriate transformations for parametric tests, or (2) nonparametric tests will be performed.

The between-subjects comparisons among the three groups will be performed using one-way analyses of variance with Tukey-Kramer post hoc tests or Kruskal-Wallis tests with Mann-Whitney *U* tests adjusted with the Bonferroni correction. The within-subjects comparisons of the pre- and post-intervention measurements will be performed by either paired *t* tests or Wilcoxon signed-rank tests. Furthermore, the multiple regression analysis will be performed using the abovementioned covariates as predictors.

Subgroup analyses will also be undertaken among the different subpopulations defined by each of the multiple baseline characteristics of the participants in order to study whether the effects of the intervention vary across these patient characteristics.

All of the analyses will be performed in accordance with the intention-to-treat principle, and various strategies to account for any post-randomization missing data will be contemplated. However, in the sensitivity analyses, we will also perform per protocol analyses to assess the robustness of our findings with regard to potential incomplete adherence; in particular, patients with major protocol violations or poor adherence will be excluded.

All statistical analyses will be performed using the IBM SPSS Statistics Package v21 (IBM, Armonk, NY, USA). A *p* value of <0.05 will be considered statistically significant.

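### Centre is neither a stratum in the randomisation nor a term in the planned between-group analysis, so chance centre imbalance stays in the treatment comparison

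*Protocol article*

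**What the plan says.** The section on randomization in the protocol article sets its aim as follows: "Balanced allocation of participants to each group will be achieved using the following method". The method is a single trial-wide list: "300 random allocation numbers with no overlap and no underlap will be generated by the" spreadsheet random-number and rank functions. One third of the randomly ordered numbers goes to each arm. The envelopes are then distributed: "The 300 envelopes will be divided 30 by 30 for ten centers in sequence". No blocks and no centre strata are described. The article attaches its own condition to equality of the arms: "Once the 300 participants have been completely allocated, the number of participants in each of the three groups will be equal".

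The section on interim analyses says "Interim analyses of the trial will be performed when 100 and 200 participants have completed the trial", and it allows stopping for harm, benefit or futility.

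The Statistical analysis section says "The between-subjects comparisons among the three groups will be performed using one-way analyses of variance with Tukey-Kramer post hoc tests", or Kruskal-Wallis tests with Bonferroni-corrected Mann-Whitney tests. It adds a multiple regression on the covariates named earlier. The Covariates section lists participant characteristics (oral, denture-related, sociodemographic, medical and anthropometric) and oral dryness. Centre is not on that list.

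**The concern.** Centre can be handled in the design by stratifying the randomisation, in the analysis by adjusting for it, or both. As described, this plan does neither.

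Centre could plausibly matter. Each centre has its own coordinator and evaluators (Organization section), and its own dentists treat denture problems during the trial (Trial schedule). The primary outcome is a self-rated visual analogue scale in unblinded participants. If mean ratings differ between centres, two things follow under a one-way analysis:

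- Between-centre variation stays in the error term and widens the confidence intervals.
- A centre with high ratings that happens to hold more of one arm shifts the arm contrast by chance.

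What is at stake is precision and the chance error of a single realised allocation. The validity of the test is not in question.

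**Working it through.** **Inputs.** 300 envelopes, 3 arms of 100, and 10 centres of 30 (Randomization section); possible stopping at 100 or 200 completers (Interim analyses section); 100 per group including 10% dropout (Sample size calculation).

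**Step 1: the plan's own figure.** 300/3 = 100 per arm and 300/10 = 30 per centre. The equal arms at full allocation are reproduced.

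**Step 2: balance within a centre.** The 30 cards are a draw without replacement from 100/100/100. For one arm:
- Mean = 30 × 100/300 = 10.
- SD = √[30 × (1/3) × (2/3) × (300 − 30)/(300 − 1)] = √6.02 = 2.45. The 95% range is about 5 to 15.
- P(exactly 10 in a given arm) = 0.161.
- P(6 or fewer, or 14 or more) = 0.152.
- P(exactly 10:10:10) = C(100,10)³ / C(300,30) = 0.030.

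In 40,000 simulated lists the mean gap between the largest and smallest arm in a centre was 5.1. On average 3.9 of 10 centres had a gap of 6 or more. The worst centre's gap averaged 9.5 and was at least 8 in 86% of lists.

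**Step 3: overall balance if the list is not finished.** Opened envelopes are treated as a random subset of the list.

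| Envelopes used | SD of one arm | Mean gap, largest to smallest arm | 95th percentile |
|---|---|---|---|
| 100 | 3.86 | 8.0 | 16 |
| 200 | 3.86 | 8.0 | 16 |
| 240 | 3.27 | 6.8 | 13 |
| 270 | 2.45 | 5.1 | 10 |

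These gaps cost little. The variance of a pairwise difference rises on average by about 1.5% at 100 envelopes, 0.4% at 200 and 0.1% at 270.

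**Step 4: cost of a centre term if centres do not differ.**
- Degrees of freedom: 3 × 90 = 270 completers, and 270 − 3 = 267 residual degrees of freedom. Nine centre terms leave 258.
- Precision: under random allocation, the expected share of an arm indicator explained by centre is (10 − 1)/(300 − 1) = 0.030. The variance of an arm difference therefore rises by 1/(1 − 0.030) = 1.03. Simulation of the three-arm model gives the same 1.03.

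**Step 5: gain if centres do differ.** Let R be the share of outcome variance due to centre. The documents give no value, so 0 to 20% is assumed. The adjusted-to-unadjusted variance ratio is about 1.03 × (1 − R):

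| R | Variance ratio |
|---|---|
| 0% | 1.03 |
| 3% | 1.00 |
| 10% | 0.93 |
| 20% | 0.82 |

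Break-even is at R of about 3%.

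**Step 6: cost at an early stop.** The Step 4 formula gives 1/(1 − 9/199) = 1.05 at 200 participants and 1/(1 − 9/99) = 1.10 at 100. The break-even R rises to about 5% and 9%.

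**The case against.** **The article makes no false promise.** It states the condition for equality itself and nowhere claims balance within centres. A stopping rule does not contradict a statement conditional on 300 allocations. This is correct, so the point is about method and not about a contradiction.

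**Unstratified randomisation is valid.** Chance centre imbalance is part of the sampling error that the unadjusted test allows for, and unequal totals cost almost nothing (Step 3). This also stands. A reader might infer from the imbalance figures that the comparison is biased; the documents do not support that.

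**The analysis model may be settled in a fuller plan.** An article condenses. But a one-way analysis has no place for centre by definition, and the article also names its covariates. The concern is with a method that is stated, not with a detail left out. If the full plan already adjusts for centre, the point is met.

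**The envelope wording.** A reader might infer that envelopes were stacked by arm and then cut, so that whole centres received one treatment. The text is loose about the order of the stack. But it says that the numbers are put in random order and that participants are allocated equally and randomly. An arm-sorted stack conflicts with both statements, so the ordinary reading is a randomly ordered list.

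**Re-blocking the remaining envelopes.** This may look like the natural remedy, but recruitment opened in September 2013 (Trial status). New blocks cannot give 10:10:10 where unbalanced cards have already been opened. They would also remove the overall 100:100:100 guarantee. And they would make allocation more predictable to the coordinator, who both obtains consent and opens the envelope. The objection is right, and the change belongs in the analysis alone.

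**Conclusion.** The point holds as a modest one about the analysis. Under the ordinary reading of the allocation procedure, balance within centres is left to chance, and overall equality is guaranteed only at 300. Neither causes systematic bias. The weakness is that the stated between-group test and covariate list leave out the one factor by which the envelopes were divided.

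The size depends on the unknown centre effect. Over an assumed 0 to 20% of outcome variance, adjustment changes the variance of an arm difference by a factor of 1.03 down to 0.82 at full enrolment. The small certain cost is exceeded once centre explains about 3%. At a stop after 100 participants the threshold is nearer 9%, so the case is weaker there. These figures assume about equal enrolment per centre and additive centre effects.

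**What to change.** Replace the one-way ANOVA for the between-group comparisons with a linear model containing arm and centre, and apply the Tukey-Kramer comparisons to the centre-adjusted arm means. If the nonparametric route is taken, use a rank test stratified by centre (van Elteren type), with the Bonferroni correction kept for pairwise tests. Add centre to the covariates of the multiple regression. Make the change before any between-group results are seen, and apply the same model at any interim look and in the final analysis.

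In the Randomization section, one added sentence saying that the envelopes were in random order when they were cut into thirties would remove the loose wording. Leave the envelopes as they are.

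The cost is 9 of about 267 degrees of freedom and about 3% of precision if centres do not differ. A stratified rank test that uses only the two arms being compared keeps about 95% of the information of a centre-balanced design, so its cost is a little higher. No new data are needed, because each participant's centre is already known.
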